## Abstract

**Background:**

Small cell lung cancer (SCLC) is highly invasive with poor prognosis, and its treatment has historically been hindered due to the absence of targetable driver genomic alterations. However, the high genomic instability and replication stress in SCLC have made poly(ADP-ribose) polymerases (PARPs) inhibitors a focus of research. Pamiparib is an orally available PARP1/2 inhibitor with high selectivity, strong PARP trapping activity, and excellent brain penetration. Utilizing pamiparib as consolidation maintenance therapy in limited-stage SCLC holds promise for improving survival outcomes and offering a viable therapeutic approach.

**Methods:**

This single-arm, open-label phase II trial will enroll patients aged 18–75 years with histologically/cytologically confirmed, limited-stage SCLC who have not progressed following definitive platinum-based cCRT and have an ECOG PS of 0 or 1. Patients will be excluded if they have histologically confirmed mixed SCLC or NSCLC, or have undergone previous tumor resection, or can be treated with surgery or stereotactic body radiation therapy/stereotactic ablative radiation therapy. Participants will receive pamiparib 40 mg twice daily every 3 weeks within 2 to 6 weeks after cCRT for up to 1 year or until disease progression according to RECIST v1.1. The primary endpoint is the 1-year progression-free survival (PFS) rate assessed by investigators per RECIST v1.1. Secondary endpoints include PFS, objective response rate, and duration of response assessed by investigators per RECIST 1.1, overall survival, time to distant metastasis, and safety.

**Discussion:**

The study will provide valuable data on the feasibility, safety, and effectiveness of pamiparib as a consolidation therapy after cCRT in patients with LS-SCLC. The correlation between molecular typing or gene expression profile of the disease and curative response will be further explored.

**Trial registration:**

NCT05483543 at clinicaltrials.gov.

## Background

Small-cell lung cancer (SCLC) accounts for 14% of newly diagnosed lung cancer cases and is characterized by its high invasiveness, early metastasis, and poor prognosis. Although the incidence of SCLC has declined in most age groups, the median overall survival (mOS) has shown minimal improvement over the past three decades, remaining stagnant at 7 months [1, 2]. Limited-stage (LS) SCLC is defined as lesions that can be included in a single radiation field. Currently, approximately 30% of SCLC patients are initially diagnosed with LS. The standard treatment is thoracic radiotherapy (DT60-66 Gy/33 Fx, 2 Gy/Fx or DT45 Gy/30 Fx, 1.5 Gy bid) in combination with 4 courses of cisplatin/carboplatin plus etoposide chemotherapy (National Comprehensive Cancer Network®) [3]. Despite the initial high response in the first-line treatment of LS-SCLC, relapse inevitably occurs with only approximately 10% of patients maintaining a disease-free status after 2 years [4]. Multiple maintenance therapies, including immunotherapy, targeted therapy, and chemotherapy-based combination therapy, have been studied, yet their effectiveness remains constrained [5–7]. While some studies have reported marginal enhancements in PFS, the OS data from almost all trials have demonstrated negative results [8, 9]. More effective approaches that could delay disease recurrence and improve outcomes for SCLC patients after the initial treatment are needed.

Poly (ADP-ribose) polymerase (PARP) is a diverse family of enzymes involved in ADP-ribose transfer, with PARP-1 and PARP-2 playing critical roles in the DNA damage response (DDR) [10]. Ovarian and breast cancers with BRCA mutations suffer from deficiencies in the homologous recombination (HR) pathway, making them highly susceptible to the synthetic lethality induced by PARP inhibitors (PARPi). This forms the fundamental basis for their current application in anticancer therapy [11]. Even beyond the HR-related context, PARPi itself acts as a DNA-damaging agent by capturing PARP1, resulting in the accumulation of single-stranded DNA (SSD) and impeding the progression of DNA replication forks, ultimately leading to the formation of DNA double-strand breaks (DSBs) [12].

Preclinical studies and genomic/transcriptomic analyses have revealed the vulnerability of SCLC to PARP inhibitors. Firstly, SCLC cell lines and tumors show significantly higher levels of PARP1 protein and mRNA compared to healthy lung tissue and other types of lung cancer [13]. Secondly, despite SCLC tumors naturally having the ability for homologous recombination (HR), preclinical data still strongly indicate their remarkable responsiveness to PARPi [14, 15]. This sensitivity could be attributed to the distinct biological features of SCLC’s DNA replication stress. Several factors, including the inactivation of tumor suppressor genes p53 and RB1, amplification of the MYC family, ongoing abnormal cell growth and metabolism [16–18], accumulation of reactive oxygen species (ROS) within cancer cells [19, 20], and unconventional protein post-translational modifications [21], collectively define the distinctive biological nature of DNA replication stress in SCLC. Furthermore, PARPi has also been proven to be an effective chemoradiosensitizer, significantly increasing mortality in various tumor models [22, 23]. Clearly, PARPi demonstrates significant potential in treating SCLC, given its primary pharmacological action targeting DNA replication, which is in line with the biological features of SCLC and its sensitivity to radiotherapy and chemotherapy. The alignment between PARPi and the heterogeneous biological characteristics and treatment strategies of SCLC undoubtedly provides strong support for conducting further clinical trials.

Pamiparib is a potent small molecule inhibitor of PARP-1 and PARP-2, showing superior cytotoxicity compared to other PARP inhibitors. Notably, it exhibits exceptional blood-brain barrier (BBB) permeability in mouse models, enabling effective penetration into the central nervous system (CNS) for tumor therapy [24, 25]. Conditional approval has been granted by the China National Medical Products Administration (NMPA) for treating patients with recurrent advanced ovarian cancer carrying germline BRCA mutations after at least two lines of chemotherapy [26]. Promising efficacy with acceptable tolerability has been demonstrated in preclinical studies and clinical trials for a range of solid tumors, including ovarian, breast, and lung cancers [27–30].

Building upon this foundation, we conducted a phase II, single-arm, prospective study to assess the efficacy and safety of pamiparib as a monotherapy maintenance treatment and investigate its mechanism of action in local-staged small cell lung cancer, with the aim of providing improved therapeutic options for patients. Furthermore, this study will facilitate discussions surrounding optimal drug utilization, patient selection criteria, and timing of pamiparib treatment in limited-stage small cell lung cancer.

## Methods and design

### Study design

This study is a prospective, single-arm, phase II clinical trial, with 1-year PFS as the endpoint, to evaluate the efficacy and associated toxicity of Pamiparib as single-agent consolidation treatment in patients with LS-SCLC who have not progressed following platinum-based concurrent chemoradiotherapy (cCRT). This protocol was approved by the ethics committee of Fudan University Shanghai Cancer Centre (Ethics number: 2206255-15) and registered on clinicaltrials.gov as NCT05483543. A flowchart of the study design is depicted in Fig. 1.

**Fig. 1 Fig1:**
[figure not shown]
Flowchart of the study. *ECOG* Eastern Co-operative Oncology Group, *MRI* magnetic resonance imaging, *CT* computed tomograph

### Objectives

#### Study endpoints

*Primary endpoint*

1-year progression free survival rate, the percentage of patients who did not experience disease progression as defined by response evaluation criteria in solid tumors (RECIST) v1.1 or death due to any cause within 1 year from the date cCRT treatment ended.

*Secondary endpoints*

Progression-free survival according to RECIST v1.1 from date of cCRT treatment ended until the date of first documented progression or date of death from any cause, whichever came first, assessed up to 24 months. For patients whose disease did not progress, PFS was evaluated by censoring patients at their most recent imaging.Overall survival from date of cCRT treatment ended until the date of end of treatment visit or date of death from any cause, whichever came first, assessed up to 24 months. Participants still alive at the time of data analysis will be censored at the date of last follow-up.Overall Response Rate quantifies the proportion of patients with measurable baseline lesions achieving a complete response or partial response as per RECIST 1.1 criteria.Duration of Response measures the time from the first documented objective response according to RECIST 1.1 criteria to disease progression or death from any cause, including only patients achieving objective response.Distant Metastasis-Free Survival is the interval from the completion of cCRT until the first occurrence of distant metastasis or death from any cause, incorporating metastases such as separate tumor nodules in contralateral lung lobes, tumor with nodules or malignant effusions involving the pleura or pericardium, or extrathoracic metastases.The level of AEs defined by NCI-CTCAE v5.0. Safety assessments will be assessed and documented after initiation of study drug, regardless of relationship to study drug.

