#### Eligibility criteria

*Inclusion criteria*

The patient or a legally authorized representative must provide study-specific informed consent prior to study entry, had good compliance, and cooperated with the follow-up.Age at least 18 years.Pathologically (histologically or cytologically) proven diagnosis of limited stage small cell lung cancer (Stage Tx, T1-T4, N0-3, M0, American Joint Committee on Cancer staging, 8th edition), within 60 days prior to registration.Patients must have measurable disease (per Response Evaluation Criteria in Solid Tumors [RECIST], version 1.1) prior to the required cycle of cCRT.Patients must be free of disease progression and not be able to receive other antitumor therapy within 6 weeks of completion of cCRT.Patients must submit archived or freshly biopsied tumor tissue (formalin-fixed, paraffin-embedded tissue block or approximately 15 unstained sections [must have > 8 sections]) along with the relevant pathology report.Eastern Cooperative Oncology Group (ECOG) performance status of 0–2 within 30 days prior to registration.Patient life expectancy must be > 12 weeks.

*Exclusion criteria*

Mixed SCLC or NSCLC confirmed by histology.Previous tumor resection for LS-SCLC.Any patient treatable by surgery or stereotactic body radiation therapy/stereotactic ablative radiation therapy should be excluded.Expected to receive any other form of anti-tumor therapy during the study period.Previous treatment with PARP inhibitor drugs.Any active malignancy within 2 years prior to enrollment, excluding the specific cancers being studied in this study and locally recurrent cancers that have been cured (e.g., resected basal or squamous cell skin cancer, superficial bladder cancer, cervical cancer carcinoma in situ or carcinoma in situ of the breast).Women who are pregnant, breastfeeding, or planning to become pregnant during the study.Concurrent participation in another therapeutic clinical trial.

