#### Pamiparib

In patients who have not progressed after concurrent chemoradiotherapy, Pamiparib will start treatment within 2–6 weeks after concurrent chemoradiotherapy as determined by the investigator. The recommended clinical current routine use dose is 40 mg (2 capsules), 2 times a day, orally; Continue dosing for up to 12 months or until RECIST version 1.1-defined disease progression, unacceptable toxicity, death, or another discontinuation criterion, whichever occurs first.

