### Sample size calculation

This study will conduct a single-arm, phase II clinical trial in patients with LS-SCLC who have not progressed after platinum-based cCRT. Selected patients will receive consolidation therapy with pamiparib monotherapy, with 1-year PFS as the end point of the study to evaluate the efficacy and related toxicity of pamiparib consolidation therapy. In previous studies of cCRT in LS-SCLC, the 1-year PFS rate was only 43.8–52.8% [31–33]; patients received tarazopanib 1.0 mg/d, and the median PFS was 11.1 weeks [34]. We presupposed that the study protocol would increase PFS from 45 to 60%, α = 0.1, and 39 patients were expected to be enrolled, and 10% dropout was considered, and a total of 44 patients were enrolled. The final analysis of PFS was estimated to be approximately 12 months after the last patient was enrolled to ensure mature PFS data and long-term safety follow-up.

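### The 1-year PFS clock starts at the end of cCRT, but pamiparib starts 2–6 weeks later and only in non-progressors, so the treated cohort's rate includes event-free time guaranteed by design; the benchmark's clock is not stated.

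*Protocol article*

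**What the plan says.** All from the protocol article:

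- **Study endpoints, primary.** The 1-year rate counts patients without progression "or death due to any cause within 1 year from the date cCRT treatment ended".
- **Study endpoints, secondary.** PFS uses the same origin: "Progression-free survival according to RECIST v1.1 from date of cCRT treatment ended until the date of first documented progression". OS and distant metastasis-free survival (DMFS) also run from the end of cCRT.
- **Pamiparib.** In patients who have not progressed, "Pamiparib will start treatment within 2–6 weeks after concurrent chemoradiotherapy as determined by the investigator".
- **Eligibility criteria.** "Patients must be free of disease progression and not be able to receive other antitumor therapy within 6 weeks of completion of cCRT".
- **Sample size calculation.** The trial is a "single-arm, phase II clinical trial in patients with LS-SCLC who have not progressed after platinum-based cCRT". The benchmark is introduced with "In previous studies of cCRT in LS-SCLC, the 1-year PFS rate was only 43.8–52.8" per cent. The plan assumes that treatment "would increase PFS from 45 to 60" per cent, with α = 0.1, 39 patients, and 44 after 10% dropout.

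The article describes no landmark, no delayed-entry analysis and no clock from enrolment or first dose.

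**The concern.** A patient who progresses or dies between the end of cCRT and the planned first dose never joins the treated cohort. Everyone who does join has already survived 2–6 weeks without progression, and those weeks count towards the 1-year rate although no study drug was taken. With a year of 52.18 weeks, only about 46 to 50 weeks of the window are truly at risk.

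There is no control arm to carry the same guaranteed time, so the efficacy conclusion rests on one observed rate set against 45%. If that 45% comes from cohorts without the same guaranteed time, part of any apparent gain comes from the definition and not from pamiparib. The start date is left to the investigator within the window, so the amount of guaranteed time also varies between patients.

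**Working it through.** **The plan's own figure.** 39/0.9 = 43.3, rounded up to 44, so the dropout step reproduces. The 39 cannot be checked fully, because power, sidedness and accrual time are not stated. This point does not depend on it.

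**Inputs from the article.** Clock origin: end of cCRT. First dose: t0 = 2 to 6 weeks later, progression-free. Null rate 0.45, target 0.60, n = 39.

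**Assumptions, not in the article.** The benchmark is unselected and timed from the end of cCRT, the drug is inert, and the hazard is Weibull: S(t) = 0.45^((t/52.18)^k), t in weeks. k = 1 is constant hazard, k > 1 means few early events, and k < 1 means many.

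**Step 1: direction.** Among patients event-free at t0, the protocol's rate is S(52.18)/S(t0).
- S(t0) ≤ 1, so this is at least S(52.18), the unselected cohort's rate on the same clock.
- The same patients' 1-year rate from first dose is S(52.18 + t0)/S(t0), which cannot exceed S(52.18)/S(t0).

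Both statements hold for any hazard shape.

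**Step 2: size.** The inert-drug rate is 0.45^(1 − (t0/52.18)^k).

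| Weibull shape k | t0 = 2 wk | 4 wk | 6 wk |
|---|---|---|---|
| 0.8 | 47.7% | 49.9% | 51.8% |
| 1 | 46.4% | 47.8% | 49.3% |
| 1.5 | 45.3% | 45.8% | 46.4% |
| 2 | 45.05% | 45.2% | 45.5% |

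For example, with k = 1 and t0 = 6 weeks, S(t0) = 0.912 and 0.45/0.912 = 0.493. Under constant hazard the excess is 1.4 to 4.3 points, or 9% to 29% of the planned 15-point gain.

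**Step 3: effect on a test.** The article gives no decision rule. As an illustration, take success as at least 23 of 39, the smallest cut-off whose exact binomial size at 45% is no more than 0.10. That size is 5.6%.

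| Weibull shape k | t0 = 2 wk | 4 wk | 6 wk |
|---|---|---|---|
| 0.8 | 10.6% | 16.4% | 23.3% |
| 1 | 7.9% | 10.9% | 14.8% |
| 1.5 | 6.0% | 6.8% | 7.9% |
| 2 | 5.7% | 5.9% | 6.3% |

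**Step 4: a different benchmark clock.** Suppose instead that the benchmark counted from the start of chemotherapy, with 12 weeks of cCRT (four three-week cycles) free of events and a constant hazard after that. The weekly hazard is −ln(0.45)/(52.18 − 12) = 0.0199. On the protocol's clock an inert drug then shows exp(−0.0199 × (52.18 − t0)) = 36.9%, 38.4% or 39.9% for t0 = 2, 4 or 6 weeks. This is below 45%, and at least 23 of 39 would be reached with probability 0.4% to 1.3%.

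**Step 5: can 45% stay after moving the clock?** Under Step 2's assumptions the inert-drug rate from first dose is S(52.18 + t0)/S(t0). For k = 1 this is exactly 45%. For k = 2 it is 42.3% to 37.5%, and for k = 0.8 it is 46.6% to 48.2%. The null therefore carries over unchanged only if the hazard is constant.

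**The case against.** The strongest reply is that bias against 45% depends on sources the article only cites. The sample size section does not say where those studies started the clock or whether they were limited to non-progressors. If they used non-progressors with the same clock, the comparison is fair. If they counted from the start of treatment, the net direction can reverse, as Step 4 shows. This stands. It limits the claim about 45%, but it does not touch the comparison with PFS from first dose.

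Second, early events may be rare after a treatment that the Background describes as having a high initial response, and the effect would then be close to nil. This also stands, which is why a range is given.

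Third, a reader might infer that no enrolled patient can have an event in the gap. The text does not settle this. The Eligibility criteria ask for diagnosis within 60 days before registration, which is shorter than four three-week cycles (84 days). The Radiotherapy section places a radiation oncologist's review ahead of enrolment. Both suggest registration before cCRT ends, whereas the Abstract, Study design and Sample size sections describe patients who have already completed it. Patients registered early could have events in the gap. The guaranteed time belongs to the dosed, progression-free cohort, and the article does not make clear whether that cohort is the denominator.

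Finally, a shift of 1.4 to 4.3 points is smaller than the 9-point spread of the cited benchmark (52.8 − 43.8). That is true, but the spread is uncertainty about the comparator, whereas the shift comes from a definition the sponsor can change.

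**Conclusion.** The point holds in a limited form. In the treated cohort, the stated clock gives a 1-year rate at least as high as the same patients' 1-year PFS from first dose, and at least as high as that of an unselected cohort with the same hazard timed from the end of cCRT. That direction needs no distributional assumption.

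The size does need one. With an unselected benchmark timed from the end of cCRT, an inert drug would show 46.4–49.3% under constant hazard, and about 45.1–51.8% across the Weibull shapes tried. Under the illustrative rule of at least 23 of 39, the false-positive rate would be 7.9–14.8% under constant hazard and 5.7–23% across the range, against 5.6% without the effect.

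Two stronger readings are tempting. One is that the stated α = 0.1 fails. The article gives no decision rule, test or benchmark origin, and several of the illustrative values stay below 0.10. The other is that 45% can be kept once the clock moves to first dose. That would need a benchmark timed from the end of cCRT and a constant hazard, and the article supports neither.

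**What to change.** 1. Start the clock for the primary 1-year rate and for PFS at the first pamiparib dose, or at registration if that follows the post-cCRT assessment. Align OS and DMFS for consistency; the sample size section sets no test on them.
2. Keep the end-of-cCRT clock as a sensitivity analysis, with delayed entry (left truncation) at first dose.
3. State the time origin and patient selection behind the 45%, and re-derive the null on the same origin and population as the trial's endpoint.
4. Reconcile the 60-day diagnosis rule and the pre-enrolment radiotherapy review with the sections that place entry after cCRT, and say whether registered or dosed patients form the denominator.

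Cost: a change of definition plus work on the benchmark. It needs no extra patients, only the date of first dose. The observed 1-year rate becomes slightly less favourable. If patients are enrolled before first dose, follow-up for the last of them runs up to 6 weeks longer.

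### The overall survival definition ends at the end-of-treatment visit as well as at death, which contradicts its own 24-month window and, read literally, leaves out deaths after that visit

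*Protocol article*

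**What the plan says.** OS is defined in one place only, among the secondary endpoints under Study endpoints; the abstract merely lists it. The item has three parts:

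- **Start and end:** "from date of cCRT treatment ended until the date of end of treatment visit or date of death from any cause, whichever came first".
- **Window:** the same sentence goes on to say that OS is followed for up to 24 months.
- **Censoring:** "Participants still alive at the time of data analysis will be censored at the date of last follow-up".

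The section on pamiparib fixes when treatment, and so the end-of-treatment visit, can occur. For the start: "Pamiparib will start treatment within 2–6 weeks after concurrent chemoradiotherapy". For the stop: "Continue dosing for up to 12 months or until RECIST version 1.1-defined disease progression, unacceptable toxicity, death, or another discontinuation criterion", whichever is earliest.

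The other time-to-event endpoints in the list (PFS, duration of response and distant metastasis-free survival) end only at a disease event or death. OS alone ends at an administrative visit.

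**The concern.** A patient who stops pamiparib alive reaches the end-of-treatment visit before dying. Taking the earlier of visit and death then closes that patient's OS at the visit, whatever happens later. The text does not say whether reaching the visit is an event or a censoring, and neither reading measures survival.

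The distinction matters for this trial's own argument. The Background says that maintenance trials in this disease sometimes improved PFS slightly while almost none improved OS. The Discussion says the same of olaparib maintenance, and hopes for a survival benefit from pamiparib. An OS endpoint that loses deaths after treatment cannot speak to that question. The contradiction also leaves an analyst to choose between two rules, possibly with the data in hand.

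**Working it through.** The plan gives no OS figure to reproduce. The check sets the parts of the definition side by side and works out what the literal rule allows.

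**1. Latest closing time under the literal rule**

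Inputs, all from the section on pamiparib: start 2 to 6 weeks after chemoradiotherapy; dosing for 12 months at most. Time zero for OS is the end of chemoradiotherapy. With 30.44 days per month:

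- start at 2 weeks: 14 / 30.44 = 0.46 months; 12 + 0.46 ≈ 12.5 months
- start at 6 weeks: 42 / 30.44 = 1.38 months; 12 + 1.38 ≈ 13.4 months

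The article gives no timing for the visit, so any lag L between last dose and visit is added: the limit is 12.5 + L to 13.4 + L months.

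**2. Comparison with the stated window**

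With L = 0, 24 − 13.4 = 10.6 to 24 − 12.5 = 11.5 months of the 24-month window could never be used. The window makes sense only if follow-up runs past the visit.

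**3. Does the censoring sentence repair the definition?**

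| Patient | Literal end-point rule | Censoring sentence |
|---|---|---|
| Dies before the visit | Counted at death | Does not apply |
| Passes the visit, alive at analysis | Closed at the visit | Censored at last follow-up: conflict |
| Passes the visit, dies before analysis | Closed at the visit, death not counted | Does not apply |

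The sentence conflicts with the rule in the second row. It says nothing about the third, where the deaths are lost.

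**4. Event or censoring?**

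- *Event:* the endpoint is time to the end-of-treatment visit or death.
- *Censoring:* progression is one of the stopping reasons, so patients would be removed when their risk of death rises. That breaks the independent-censoring assumption of a Kaplan–Meier estimate.

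**5. How many could be closed near progression in year one?**

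Input from Sample size calculation: the plan "would increase PFS from 45 to 60%, α = 0.1". At the target, 1 − 0.60 = 0.40 have a PFS event by one year, or 0.40 × 44 = 17.6 of the 44 planned patients. PFS events include deaths, and a patient whose first event is death has OS recorded correctly. So 40% is an upper bound for those closed near progression. At the 45% reference rate the bound is 1 − 0.45 = 55%.

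**6. Illustration only**

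The documents give no OS figure, so these are assumptions: exponential times to progression and death before progression; 1-year PFS of 45% or 60%; 10% of PFS events are deaths; median OS of 20 to 40 months; visit at progression or at 12.5 or 13.4 months. In simulation, 28% to 59% of patients die by 24 months (about 12 to 26 of 44). Only 4% to 6% (about 2 to 3 of 44) die before the visit and would be counted. Other assumptions give other numbers, and the finding does not depend on them.

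**The case against.** The strongest reply is that ordinary OS was intended and the visit is a stray phrase. The 24-month window and the censoring of survivors at last follow-up both presuppose follow-up after treatment, which ends by about 13 months. This is the likelier account of intent, and it stands. A reader might infer from the end-point clause that the sponsor chose to stop measuring survival at end of treatment, or that later deaths will go unrecorded. The documents do not support that. They show a definition at odds with itself, not a decision to end follow-up. The reply still does not remove the defect: the only stated definition gives a wrong result for a patient who dies after the visit, and the censoring sentence does not reach that patient.

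A reader might also infer that OS would simply become PFS. That goes too far. At the target, 60% are progression-free at one year. Patients still on treatment would be closed at the treatment limit, and those who stopped for toxicity or another reason at the visit that followed; neither is a PFS event. Nor do the documents give a rate of death on treatment that would show how many patients reach the visit alive.

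Finally, OS is one of several secondary endpoints in a single-arm trial with no stated OS test or target. That stands too, and limits the weight of the point.

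**Conclusion.** The OS item is wrong as written and contradicts itself. Followed literally, it closes OS no later than about 12.5–13.4 months plus an unstated lag to the visit, against a stated window of 24 months, and leaves out deaths after the visit. At most about 40% of patients would have OS closed near progression in the first year, if the 60% target holds. The closing time rests only on the dosing limits in the article; the 40% rests on the design target and is an upper bound.

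A reader might infer that the defect threatens the trial's main conclusion. It does not: the 1-year PFS rate has its own definition, the sample size rests on that rate, and neither uses OS. The point should be fixed, but it is not grave for the trial as a whole.

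**What to change.** Define OS as the time from the end of chemoradiotherapy to death from any cause. Delete the end-of-treatment visit as an end point. Censor patients not known to have died at the date last known alive, within the 24-month window already stated.

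The cost is one phrase removed and the censoring sentence tightened. It changes neither the sample size nor the primary analysis, and needs no follow-up beyond the stated window. The full protocol, the SAP and the registry entry were not available for this review. They should be checked, and corrected only if they carry the same wording.
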